### Interventions

#### Tongue scraping

In Group 1, tongue scraping will be performed by the same operator in all patients. Posterior-anterior movements will be performed with a plastic scraper (Halicare®) over the lingual dorsum, followed by cleaning of the scraper with gauze. Also, the tip of the tongue will be cleaned with another piece of gauze in order to remove the tongue coating that could be accumulated in this area. This procedure will be performed ten times in each patient in order to standardize the mechanical removal of the coating. In the groups in which we use tongue scrapers (Groups 1 and 3), the scrapers will be given to the patients, and they will be instructed to use them every night. Data on whether they use the scraper regularly will be collected on the 7 days control, so the effect of tongue scraping can be checked as well as the compliance of patients to this technique.

#### Antimicrobial photodynamic therapy (aPDT)

Group 2 will be treated with aPDT. The LED light curing device Valo Cordless Ultradent®, an office appliance, with a coupled radiometer, and a spectrum of 440–480 nm will be used. Both the volunteer to be treated and the professional will be using specific eye protection glasses. The active end of the LED will be coated with clear disposable plastic (PVC), thus avoiding cross contamination. One session of aPDT with *Bixa orellana* extract in spray will be performed. *Bixa orellana* extract manipulated at a concentration of 20% (Fórmula e Ação®) will be applied in a sufficient amount to cover the middle third and back of the tongue. Following 2 min of pre-irradiation time, six points in the tongue dorsum with a distance of 1 cm between them will be irradiated. The apparatus will be pre-calibrated at wavelength 395–480 nm for 20 s and 9.6 J of energy per point, which is similar to the energy used in other protocols of aPDT in the tongue that have had satisfactory results [7, 15–17]. Table 1 shows all the parameters that shall be used. The energy of 9.6 J per point is similar to the energy used in other protocols of aPDT in the tongue that had satisfactory results [7, 15–17], which is why we are maintaining this parameter.

**Table 1 Tab1:** LED parameters to be used in this study

Wavelength (nm)	395–480
Operating mode	Continuous wave
Average radiant power (mW)	480
Polarization	Random
Aperture diameter (cm)	0.9
Irradiance at aperture (mW/cm^2^)	762
Beam profile	Top hat
Beam spot size at target (cm^2^)	3.14
Irradiance at target (mW/cm^2^)	153
Exposure duration (s)	20
Radiant exposure (J/cm^2^)	6.37
Radiant energy (J)	9.6
Number of points irradiated	6
Area irradiated (cm^2^)	18.8
Application technique	Contact
Number and frequency of treatment sessions	1
Total radiant energy (J)	57.6

In Group 3, patients will receive tongue scraping performed by the same operator with instructions to perform the tongue scraping as described in Group 1, and also aPDT with *Bixa orellana* extract as described in Group 2.

### Outcome measures

#### Halimetry

Oral air collection will follow the Oral Chroma™ manufacturer’s guidelines. The participant will be instructed to rinse with a cysteine solution (10 mM) for 1 min and then remain with his/her mouth closed for 1 min. A syringe from the same manufacturer for collection of mouth air will be introduced into the patient’s mouth. For 30 s the patient will remain with his/her mouth closed, breathing through the nose, without touching the syringe with the tongue. The plunger will be pulled out, re-emptied into the patient’s mouth and pulled out again to fill the syringe with the breath sample. We will place the gas injection needle in the syringe and adjust the plunger to 0.5 ml. The collected gases will be injected into the entrance door of the unit in a single movement. This procedure will be carried out in all of the groups before treatment, immediately after treatment and after 7 days for comparison of the levels of VSCs.

To avoid changes in the halimetry, participants will be instructed to follow these instructions: 1. 48 h before evaluation, avoid ingesting food with garlic, onion or strong seasoning, alcohol consumption and the use of mouthwashes; 2. on the day of the evaluation, do not eat 2 h before the exam; abstain from coffee, candies, chewing gum and oral hygiene products; and perform teeth brushing only with water. In order to make the evaluations more similar, all patients will be scheduled in the afternoons, at approximately the same time, following the same instructions, so we can minimize variations. In addition, patients will be submitted to a brief anamnesis. Data will be collected about past and current health conditions, the use of dental floss, frequency of tooth brushing, tongue cleaning habits and the use of mouthwashes. These data will be collected in the baseline appointment and confirmed in the 7 days follow-up.

Two calibrated operators will also evaluate the presence of tongue coating. They will be trained and submitted to exercises in order to grade the presence of coating. These exercises will be conducted with 40 pictures, which will also be graded by a benchmark examiner who is specialized in halitosis and will provide the theoretical explanation before the training. The intra-examiner calibration will be performed with an interval of 2 days. A grade “0” will be awarded in cases where no coating can be seen; “1/3” in cases where only the posterior third of the tongue is covered with coating; “2/3” in cases where the posterior and middle thirds of the tongue are covered with coating; and “3/3” in cases where the whole dorsum of the tongue is covered with coating [28].

#### Microbiological analysis

The microbiological analysis of tongue coating will be performed by collecting biofilm samples from the region of the lingual dorsum with a 1-μl inoculation loop. Samples will be transferred into individual vials containing 1.5 ml of reduced transport fluid and placed in the vortex for approximately 30 s. After homogenization, the ten-fold dilution series will be prepared in 180 μl of sterile phosphate-buffered saline (PBS) solution and 10^− 2^, 10^− 3^, 10^− 4^ and 10^− 5^ aliquots and transferred to blood agar plates. Considering that the main bacteria responsible for the production of VSCs are Gram-negative and anaerobic, plaques will be incubated in an anaerobic jar for 72 h at 37 °C, for later counting of the colony-forming units (CFUs). This procedure will be performed before, immediately after and 7 days after treatment.

### Harms

The participants will be treated at the university, to make it easier for them to return, avoiding absences. No adverse effects are expected from any of the treatments.

### Statistical analysis

Data from Oral Chorma™ will be analysed for their normality by the Shapiro-Wilk test. If the normality hypothesis is accepted, the analysis of variance (ANOVA) followed by the Tukey test will be used when necessary to perform the between-groups analysis. To analyse the results of the treatment in both periods of the study, the *t* test for paired data will be used. If the normality hypothesis is rejected, the Kruskal-Wallis test followed by the Student-Newman-Keuls test, when necessary, will be used. To analyse the results of each treatment in both periods of the study, the Wilcoxon test will be used.

The kappa test will also be used to check interrater reliability in the evaluation of the presence of tongue coating.

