### Participants

Students and employees from the Universidade Nove de Julho will be screened, and 39 subjects who fulfil the inclusion and exclusion criteria will be selected to participate in this research.

The inclusion criteria are as follows: patients of both genders, from 18 to 25 years old, who present a volatile sulphur compounds (SH_2_) ≥ 112 ppb measured using the Oral Chroma™.

The exclusion criteria are as follows: individuals with dentofacial anomalies (such as cleft lip or cleft palate), who are undergoing orthodontic and/or orthopaedic treatment, who have periodontal diseases (such as gingivitis or periodontitis) or dental cavities, who are undergoing oncological treatment, with systemic alterations (gastrointestinal, renal, hepatic), who have undergone antibiotic therapy up to 1 month before the survey, who are pregnant or who are smokers.

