### Sample composition

To calculate the sample size, the data from the article by Costa da Mota et al. [21] were used. We established an error $$ err=\left|\overline{x_1}-\overline{x_2}\right| $$, where $$ \overline{x_1} $$ and $$ \overline{x_2} $$ are the baseline values for periodontal treatment with aPDT. From this error, the effect size was calculated, given by:$$ \frac{err}{\sqrt{\sigma_1^2+{\sigma}_2^2}} $$where $$ {\sigma}_1^2 $$ and $$ {\sigma}_2^2 $$ are the variances of Groups 1 and 2, respectively.

Assuming that the studied groups have a normal or approximately normal distribution, that the sample size will be sufficiently large and that a two-tailed test will be used, for a significance level α = 0.05 and maintaining the power of the test 1 – β = 0.90 we have Group 1: 13 patients, Group 2: 13 patients, Group 3: 13 patients.

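### The between-group ANOVA is valid but has no baseline term, so a 13-per-group trial gives up precision that the baseline Oral Chroma value could supply

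*Protocol article*

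**What the plan says.** The Statistical analysis section of the Protocol article sets the between-group method by the result of a Shapiro-Wilk test. If normality is accepted, "the analysis of variance (ANOVA) followed by the Tukey test will be used when necessary to perform the between-groups analysis". If it is rejected, Kruskal-Wallis followed by Student-Newman-Keuls is used. No covariate, change score or group-by-time term is named for either route. Two time points are compared directly only in the within-group tests (paired t or Wilcoxon).

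Every randomised participant has a baseline value. Entry requires a sulphide level of at least 112 ppb "measured using the Oral Chroma™" (Participants). Of the breath sampling, the Halimetry section says: "This procedure will be carried out in all of the groups before treatment, immediately after treatment and after 7 days".

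The sample is "Group 1: 13 patients, Group 2: 13 patients, Group 3: 13 patients" (Sample composition). Allocation is by block randomisation, and no stratification on baseline level is described (Study design). The Discussion treats the immediate post-treatment result as the most important one, and says the trial is meant to show which of the three treatments works best.

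**The concern.** Which treatment works best is a between-group question. The within-group tests cannot answer it: everyone is selected above an Oral Chroma threshold and no arm is untreated, so a fall within a group may partly be regression to the mean. The randomised contrast carries the evidence and should be as precise as the data allow.

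If the ANOVA is run on follow-up values, stable differences between people stay in the error term, and a chance baseline difference between groups passes partly into the follow-up contrast. With 13 per group such differences are common. If the ANOVA is run on changes, baseline is used, but with a fixed coefficient of 1. That over-corrects whenever the baseline-to-follow-up correlation is below 1 (equal variances at the two times). At stake is the chance of detecting a real difference between treatments, not the false-positive rate.

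**Working it through.** **Inputs from the Protocol article.** Two-sided α = 0.05, power 0.90, 13 per group (Sample composition); three groups; baseline measured in all participants.

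**Assumed, because the article gives no figure.** Normal data with equal variance at baseline and follow-up; baseline-to-follow-up correlation ρ between 0 and 0.7; true difference 1.0 SD for one group against the others.

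**The plan's own figure.** The 13 per group cannot be reproduced, because no means, SDs or numerical effect size are given. It can be solved backwards by the normal approximation:

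d = (1.960 + 1.282) × √(2/13) = 3.242 × 0.392 = 1.27 SD,

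or 1.27/√2 = 0.90 on the article's own effect-size scale. The 1.0 SD used below is therefore somewhat smaller than the difference the sample size implies.

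**Chance imbalance.** In units of the baseline SD, the standard error of a pairwise baseline difference is √(2/13) = 0.39. A given pair differs by more than 0.5 SD with probability 20%, and at least one of the three pairs does so with probability 41% (simulated). A 0.5 SD imbalance shifts the contrast as follows:

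| ρ | Follow-up values: ρ × 0.5 | Change scores: (ρ − 1) × 0.5 |
|---|---|---|
| 0.3 | 0.15 SD | −0.35 SD |
| 0.5 | 0.25 SD | −0.25 SD |
| 0.7 | 0.35 SD | −0.15 SD |

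ANCOVA removes the shift, apart from error in the estimated slope.

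**Error variance relative to follow-up values.** ANCOVA: 1 − ρ². Change: 2(1 − ρ).

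- ρ = 0.3: 0.91 and 1.40
- ρ = 0.5: 0.75 and 1.00
- ρ = 0.7: 0.51 and 0.60

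**Power of one pairwise contrast, 3 × 13, difference 1.0 SD, simulated with the planned Tukey adjustment.** Repeat runs agree to about one point.

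| ρ | ANOVA, follow-up values | ANCOVA | ANOVA, changes |
|---|---|---|---|
| 0.3 | about 55% | about 58% | about 40% |
| 0.5 | about 55% | about 68% | about 55% |
| 0.7 | about 55% | about 86% | about 80% |

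At ρ = 0, ANCOVA loses about 2 points; at ρ = 0.2 it is about neutral. Without the Tukey adjustment, follow-up values against ANCOVA give 70% against 73%, 71% against 81%, and 70% against 93% at ρ = 0.3, 0.5 and 0.7.

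**At the implied 1.27 SD, three-group F test.** Power on follow-up values against ANCOVA is 91% against 93% (ρ = 0.3), 90% against 96% (ρ = 0.5) and 91% against 100% (ρ = 0.7).

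**Type I error.** With no true difference, all three analyses reject in about 5% of simulated trials (F test).

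**The case against.** **The analysed variable is not stated.** The stated aim is a reduction in halitosis, and the wording is compatible with an ANOVA of changes, which would use baseline. This stands: one cannot say that the plan certainly ignores baseline. It does not remove the point, because change scores did no better than ANCOVA at any correlation computed and clearly worse at 0.3 and 0.5.

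**A condensed article may leave covariates to a fuller document.** That is fair as regards silence on detail. But the article does choose the between-group test, down to the post-hoc procedures, and the choice it makes has no baseline term.

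**Unadjusted ANOVA in a randomised trial is unbiased and holds its error rate.** This stands in full. A reader might infer that the planned test yields false positives in 13% (ρ = 0.5) to 22% (ρ = 0.7) of trials. Those rates can be computed, but only for an unadjusted 5% pairwise test on follow-up values, and only given that the two groups already differ by 2 standard errors at baseline. For a given pair that happens in about 5% of randomisations. Over all randomisations the rate is about 5%, so the documents do not support calling the test invalid. Nor does validity require stratified randomisation.

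**The gain depends on an unknown correlation.** This also stands. The entry threshold truncates baseline and could lower ρ: under bivariate normality, keeping only the upper half would turn 0.5 into about 0.33 and 0.7 into about 0.51. The immediate value also follows active treatment in every arm. The figure at ρ = 0.7 is thus the favourable end of the range, not a central case. At the implied 1.27 SD the gain is smaller at ρ = 0.3 and 0.5 (2 and 6 points).

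**Conclusion.** The point holds as one of efficiency. The planned between-group tests have no baseline term, although baseline is available for everyone. They are valid but less precise than they could be, and on follow-up values they leave chance imbalance uncorrected. For a 1.0 SD difference with Tukey adjustment, ANCOVA gains about 3, 13 and 31 points of power over follow-up values at ρ = 0.3, 0.5 and 0.7. Over change scores it gains about 18, 13 and 6 points. The worst case computed is a loss of about 2 points at ρ = 0.

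These sizes rest on normal data, equal variances and assumed correlations. The direction is well supported from ρ of about 0.3 upward; the size is not known. Two stronger readings are not supported: that the analysis is invalid, and that it certainly disregards baseline.

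**What to change.** Before recruitment, which the Trial status section says has not begun, replace the between-group sentence with wording to this effect:

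- The post-treatment Oral Chroma value is compared between groups by ANCOVA, with group as factor and the baseline value as covariate (both on the log scale if skewed).
- The three pairwise contrasts (Group 2 against 1, 3 against 1, 3 against 2) are Tukey-adjusted.
- The analysis is done at the immediate time point, which the Discussion ranks first, and again at day 7.
- If a rank method is kept as fallback, it is rank ANCOVA on the baseline rank.

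This also settles which variable is analysed. The cost is one degree of freedom (35 instead of 36 for error) and a short change of wording, with no new data or visits. Specifying it now is far more credible than adding the covariate after an imbalance has been seen.

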### Hypothesis

Based on this background, this research will test the hypothesis that aPDT with *Bixa orellana* extract and blue LED is effective in the reduction of halitosis.

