### Objective

The aim of this study is to verify whether aPDT with *Bixa orellana* extract and blue LED is effective in the reduction of halitosis, providing an accessible treatment for this condition, as the majority of dentists already have this sort of device in their offices. This method will also be compared with tongue scraping, the most commonly used conventional method for tongue coating removal, and the association of both methods will also be evaluated.

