**Fig. 1 Fig1:**
[figure not shown]
Schedule of enrolment, interventions and assessments of the present study

This study has been approved by the Ethics Committee of Universidade Nove de Julho under process number 74228417.2.0000.5511. Possible changes in this project shall be reported to the committee. All participants who agree to participate voluntarily will sign an informed consent form, as stipulated in Resolution 466/2012 of the Brazilian National Board of Health. A randomized clinical trial will be conducted at the dental clinic of the Universidade Nove de Julho*.* Patients will be divided by block randomization into three groups (*n* per group = 13), according to the treatment to be performed (Fig. 2). Opaque envelopes will be identified, and a sheet containing the information of the corresponding experimental group will be inserted. The envelopes will be sealed and will remain sealed in numerical order in a safe place until execution of the procedures.

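### No controlled comparison is tied to the aPDT hypothesis: for aPDT alone, reduction is addressed only by within-arm before-after tests, with regression to the mean as a further, conditional risk

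*Protocol article*

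**What the plan says.** - **Hypothesis section:** "this research will test the hypothesis that aPDT with *Bixa orellana* extract and blue LED is effective in the reduction of halitosis". No comparator is named.
- **Objective section:** the comparison with scraping is a further aim: "This method will also be compared with tongue scraping, the most commonly used conventional method for tongue coating removal".
- **Study design section:** "Patients will be divided by block randomization into three groups" of 13. Under Interventions these are scraping (Group 1), aPDT (Group 2) and both (Group 3). None is sham or untreated.
- **Participants section:** people enter "who present a volatile sulphur compounds (SH_2_) ≥ 112 ppb measured using the Oral Chroma™". The same instrument measures the outcome.
- **Halimetry section:** readings are taken "before treatment, immediately after treatment and after 7 days for comparison of the levels of VSCs". The text does not say whether the before reading is the qualifying reading or a new one.
- **Statistical analysis section:** between groups, ANOVA with Tukey, or Kruskal-Wallis with Student-Newman-Keuls. Within groups, "To analyse the results of the treatment in both periods of the study", the paired t test, or Wilcoxon if normality is rejected. No test is assigned to the hypothesis.
- **Discussion section:** the results immediately after treatment are the ones that will show efficacy.

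**The concern.** An absolute claim that aPDT reduces halitosis needs a comparison with the same patients' course without aPDT. For Group 2 the plan has none: Group 1 and Group 3 are both actively treated, so a between-group test involving Group 2 cannot show that aPDT alone lowers H2S. What remains is the fall within Group 2, and that fall also contains anything else that happens between the two readings. A fall within Group 3 is further confounded with scraping.

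Selection on the outcome variable can make this worse. People admitted because one reading was high tend to read lower next time, treated or not. If the qualifying reading is also the baseline, a paired test will count part of that drift as a treatment effect. A reader following the plan could then report aPDT as effective when it does nothing.

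**Working it through.** **1. Which planned test bears on the hypothesis**

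| Planned test | What it can show |
|---|---|
| Paired test in Group 2 | Fall under aPDT plus everything else that changed |
| Paired test in Group 3 | Fall under aPDT and scraping plus everything else |
| Group 2 vs Group 1 | aPDT against another active treatment |
| Group 2 vs Group 3 | aPDT without and with scraping |
| Group 3 vs Group 1 | Scraping with and without aPDT, randomised |

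Only the last row isolates aPDT by randomisation. Both arms also scrape at home every night, so the contrast stays balanced on that at 7 days.

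**2. The plan's own figure.** The sample size is 13 per group at two-sided alpha 0.05 and power 0.90. No means or variances are given, so it can only be solved backwards: (1.960 + 1.282) × √(2/13) = 1.27 SD. The point does not depend on this figure.

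**3. Regression to the mean, if the qualifying reading is the baseline**

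Model with no treatment effect: reading = true value + independent error, total variance 1, reliability ρ, with a share p of screened people above the threshold c. Neither ρ nor p is in the protocol; both are assumptions. The Background section says about one third of individuals have moderate halitosis but does not link that to 112 ppb.

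- Mean qualifying reading: m = φ(c)/p. For p = 1/3, c = 0.431 and m = 1.091.
- Mean later reading: ρm. Mean fall: (1 − ρ)m. For ρ = 0.7: 0.3 × 1.091 = 0.33 SD.
- Variance of the selected readings: 1 + cm − m² = 0.280.
- Variance of the difference: (1 − ρ)² × 0.280 + (1 − ρ²) = 0.025 + 0.510 = 0.535, so SD 0.73.
- Expected t at n = 13: 0.327 / (0.732/√13) = 1.61, against a critical value of 2.18 on 12 df. A noncentral t approximation gives about 0.32.

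Simulation, one paired t test in one arm, counting only falls significant at two-sided 0.05:

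| Reliability | Top third qualify | Top half qualify |
|---|---|---|
| 0.9 | 13% | 9% |
| 0.8 | 22% | 14% |
| 0.7 | 31% | 19% |
| 0.5 | 51% | 30% |

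The nominal rate in that direction is 2.5%. At ρ = 0.7 and top third, Wilcoxon gives 29%. A false fall at either of the two follow-up times occurs in about 48% of arms, and in at least one of the six paired tests in 1 − (1 − 0.48)³ ≈ 86% of trials. With log-normal readings analysed on the raw scale (log SD 0.5 to 1.0, ρ 0.8 to 0.5, top third), the single paired t test gives 10% to 38%.

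**4. The same model with a fresh pre-treatment reading as baseline.** Baseline and later readings both have mean ρm, so the expected fall is zero. The simulated rate is about 2.5% at every setting.

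**5. Randomised comparisons under the same selection.** The three-arm ANOVA rejects in 5.0% to 5.1% and Group 3 vs Group 1 in 4.9% to 5.1%. Both keep their level.

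**The case against.** - **The between-group tests are already planned.** This stands. Tukey or Student-Newman-Keuls covers all three pairs, including Group 3 vs Group 1, and the Discussion says the techniques will be compared. A reader might infer that the trial has no controlled comparison at all, or that it will compare within-arm p-values across arms. The text supports neither. What is missing is the link from any of these contrasts to the stated hypothesis.
- **Regression to the mean is not established.** This also stands. The inflated rates need the qualifying reading to serve as baseline. The text schedules a reading before treatment and mentions a baseline appointment, and the schedule and flowchart figures, not available here, may show it to be separate. It is tempting to say that any before value taken under the same conditions would regress. Step 4 shows that this is wrong when its error is independent of the qualifying reading.
- **Choosing a primary contrast and adjusting for baseline can be left to an analysis plan.** This stands in part. The article does state both the hypothesis and the tests, however, and for aPDT alone the two do not match.
- **Group 3 vs Group 1 is not a clean test of the hypothesis.** Correct. It tests aPDT added to scraping, unblinded and with no sham spray or light in Group 1. It may also be underpowered: at 13 per arm an unadjusted t test has 90% power only near 1.33 SD, 50% at 0.8 SD and 23% at 0.5 SD. Baseline adjustment would help by an unknown amount.

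**Conclusion.** The point holds in two parts of different strength.

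The first is unconditional. With no inert arm, a within-arm fall in Group 2 cannot establish that aPDT is effective, and the plan ties no controlled contrast to the hypothesis.

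The second is conditional. If the qualifying reading is the baseline, regression to the mean alone produces a false significant fall in about 31% of null 13-patient arms at assumed reliability 0.7 with the top third qualifying. The range is about 9% (0.9, top half) to 51% (0.5, top third), against 2.5% nominal. The percentages illustrate assumed values; the direction does not depend on them. With a separate pre-treatment baseline this inflation disappears, while time, repeated rinsing and sampling, and wetting by the spray remain confounded with aPDT.

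The documents do not support saying that the trial will be inflated by regression to the mean, only that the text does not exclude it.

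**What to change.** In Statistical analysis:

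1. Name the baseline-adjusted Group 3 vs Group 1 contrast in H2S immediately after treatment (for example by ANCOVA) as the controlled test of aPDT. State that it tests aPDT as an addition to scraping, unblinded and without sham.
2. Name Group 2 vs Group 1 as the head-to-head comparison of two active treatments.
3. Label the within-arm paired tests descriptive and say that they are not evidence of efficacy.
4. State that the baseline is the treatment-day pre-treatment reading, separate from the qualifying reading.

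Items 1 to 3 are wording changes, and the trial is not yet recruiting. Item 4 is also only wording if the two readings are already separate; if they are one reading, it adds one halimetry reading per participant. No arm or patient is added.

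The price is that a within-arm fall can no longer be claimed as efficacy, and that the absolute effect of aPDT alone remains untested by this design. The hypothesis and conclusions should be worded to match.
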